### Methods: Monitoring

#### Data monitoring

A clinical research technician will be responsible for coordinating the study; specifically, the logistics and monitoring of the study, the production of reports on progress, verifying that the e-CRFs are updated, dispatch of blood samples, and notification severe adverse events (AEs) to the sponsor. The technician will follow the Standardized Operating Procedures. The data monitoring technician will be dependent towards the sponsor and independent from the study investigators. Investigators will make the data available to the persons in charge of monitoring, quality checks, or audit of the study documents, and they will provide individual data that is strictly necessary for such checking, in compliance with the legislative and regulatory conditions in force (articles L.1121–3 and R.5121–13 in the French public health code).

#### Adverse events

Any serious AEs, whether or not related to the medical object under study, expected or unexpected, must be reported within 24 h by the investigator to the sponsor on a “Serious AE” form, on which should be specified the date of occurrence, the severity rating, the intensity, the relationship with the treatment evaluated (or the study), and the outcome. All other AEs will be reported on the “AE” form in the case report form specifying the date of occurrence, the description, the severity, the duration, the method of resolution, the causal relationship, and the decisions made. The sponsor will report all suspected unexpected serious adverse drug reactions to Eudravigilance (the European pharmacovigilance database), the French Health Products Agency (Agence de Sécurité du Médicament et des Produits de Santé), and the investigators, within the regulatory time periods for reporting.

#### Auditing

The investigators agree to undergo quality assurance audits conducted by the sponsor as well as inspections performed by the competent authorities. All data and all documents and reports can be subjected to audits and regulatory inspections without limitation in relation to medical confidentiality.

### Ethics and dissemination

#### Ethics approval for the research

The sponsor and the investigators undertake to conduct this study in compliance with French law no. 2004–806 of August 9, 2004, and with Good Clinical Practice and the Helsinki Declaration (Ethical Principles for Medical Research involving Human Subjects, Tokyo, 2004). The study will be conducted in accordance with this protocol. Excluding emergency situations requiring specific therapeutic actions, the investigators will observe the protocol in all respects, particularly regarding consent and the notification and follow-up of serious AEs.

The protocol was approved on 18/08/15 by the “Comité de protection des Personnes” and received authorization from the French Health Products Agency on 27/07/15.

#### Consent

Patients will be completely and openly informed, in terms that are understandable to them, of the objectives and constraints of the study, of the possible risks incurred, of the required measures of supervision and safety, of their right to refuse to participate in the study, and of the possibility of withdrawing their consent at any time.

All this information is contained in an information and consent form given to the patient. The patients’ free, informed and written consent will be collected by the investigator, or a doctor representing them prior to final inclusion in the study. A copy of the information and consent form signed by both parties will be given to the patient; the investigator will keep the original.

#### Confidentiality and access to data

In compliance with the conditions of confidentiality of data to which individuals in charge of quality control of biomedical studies have access (article L.1121–3 in the French public health code), and with conditions pertaining to confidentiality of information, in particular concerning the type of investigational medical design, the tests, subjects in the study, and the results obtained (article R. 5121–13 in the French public health code), individuals having direct access will take all necessary precautions to ensure confidentiality of the information.

#### Dissemination policy

The data provided by the investigating centers will be analyzed by INSERM CIC 1414 Rennes. A written report on the results will be submitted to the sponsor and published on ClinicalTrials.gov.

Scientific presentations and reports corresponding to the study will be drafted under the responsibility of the coordinating investigator of the study with the agreement of the investigators in charge. Rules for publication will follow international recommendations [31]. In accordance with law no. 2002–303 of March 4, 2002, patients will be informed, at their request, of the overall results of the study.

### SPIRIT guidelines

This protocol has been written in accordance with the Standard Protocol Items: Recommendations for Interventional Trials (SPIRIT) guidelines. The SPIRIT checklist is provided in Additional file 2.

## Discussion

AD is a highly prevalent disease in both adults and children, with acknowledged unmet needs, in particular in the LTC of the disease, which has not been widely evaluated in published studies. Novel and safe therapeutic strategies are needed for long-term AD control and a potentially effective low-cost therapeutic strategy for LTC is essential for patients and public health.

The international, multi-professional initiative HOME aims to standardize and validate AD outcome measurements. LTC has been defined as a core domain to be assessed in AD studies, but the corresponding outcome measure has not yet been established and future research is needed [20]. The HOME initiative encourages the conduct of trials on LTC of AD, and cites two broad approaches to explore LTC; the first is the assessment of weeks during which the disease is well-controlled and the second is to perform serial measurements of the other three core domains (signs, symptoms, and quality of life). HOME has validated a duration of more than 3 months for future AD trials assessing LTC. Because TAT cannot be entirely withdrawn, testing ‘add-on’ therapies for LTC of AD needs both the collection of AD severity measures and an evaluation of TAT consumption. In this trial, our proposal is to evaluate AD severity by serial measurements of investigator- and patient-reported severity scores over a 2-year period, alongside TAT consumption.

Since both phototherapy and vitamin D supplementation are good candidates for LTC of AD disease activity, our proposal is to study these two treatments jointly. We will therefore use a factorial design to assess the effects of phototherapy and vitamin D supplementation on LTC within the same study; since solar exposure (and to a lesser extent artificial UV exposure under phototherapy) favors vitamin D synthesis, this design has the potential to explore the interaction between phototherapy and vitamin D supplementation in disease control and serum vitamin D levels in winter and all-year round. We have chosen a crossover design for phototherapy to adjust on personal characteristics (phototherapy and sensitivity to UV exposure being major determinants of phototherapy efficacy) [32–34]. We chose a fixed and common period for inclusion to avoid confounding by seasonality. While patients will be able to sign their written consent at any time in the pre-screening period, they will be randomized in September and we cannot exclude that some patients may drop out of the study before the randomization. The alternative would be to randomize patients throughout the year and to take into account seasonal effects, but the approach to measure this would have been complex in a study with pragmatic options and long-termfollow-up. Since we provide phototherapy sessions exclusively during winter periods, a carry-over effect is not a concern in our study.

Our trial provides the possibility of reducing topical anti­inflammatory treatment use. Further evaluation will be needed if the exploratory trial on phototherapy opens up new avenues (novel phototherapy, pro-active strategy).

As we are conducting a long-term study, we plan the following procedures to minimize attrition bias: firstly, any participant who is recommended systemic immunosuppressants will discontinue the study; secondly, our trial includes strong pragmatic options [29, 34–36] such as primary care population, standard vitamin D supplementation that is not adapted to serum levels, ‘as usual’ TAT use, and no recommendations for changes in lifestyle; thirdly, the trial includes logistic support to ensure adherence such as trained study nurses in the field facilitating participant adherence; and, finally, it will test new maintenance therapies superimposed on usual care. It can be noted that ‘add-on’ therapy trials on asthma have better rates of adherence [37].

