## Background

Atopic dermatitis (AD) is a common pruritic inflammatory skin disease that classically has a chronic course of flares and remissions. AD is a highly prevalent skin disorder, in both adults (2–10%) [1–4] and children (15–20%) [1, 5–7], and there is some evidence of an increase in AD prevalence in some regions of the world, including Western Europe [8]. Children with persistent and/or severe disease have increased AD persistence in adulthood [9].

On the severity spectrum, lower-end patients benefit from emollients and small amounts of topical corticosteroids, whereas higher-end patients need systemic immunosuppressants; in-between patients are treated with topical corticosteroids and tacrolimus (topical anti-inflammatory treatments; TAT) and phototherapy. The management of AD requires efficient control of the flares. TAT are important anti-inflammatory drugs used in AD flares. Topical corticosteroids applied on inflammatory lesional skin are widely used as a first-line treatment for disease flares. They have been evaluated in a wide variety of preparations in more than 110 different randomized controlled trials [10]. Topical calcineurin inhibitors are a second class of TAT drugs that have also proved efficacious against AD flares [11], and are administered alone or in combination with topical steroids. Phototherapy is widely used as a second-line treatment for the short-term control of moderate-to-severe AD with demonstrated efficacy, with intensive schedules of 2–7 sessions a week for 2 or 3 months [12, 13].

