These chronic in-between AD patients need large amounts of TAT to maintain control of disease activity. They certainly have the most markedly unmet medical need, with a high impact on quality of life compared to other chronic inflammatory skin diseases [14]. The major therapeutic challenge in this population is the long-term control (LTC) of disease activity, and the current TAT-basedpro-active strategy (intermittent applications of TAT after flares on previously affected skin, over long-term periods) does not meet all the needs. There is also consistent evidence of subclinical inflammation in skin of normal appearance and in the treated skin of AD patients. Similarly, there is evidence that treatments might improve this sub-clinical inflammation, prevent new flares or decrease the risk of new flares in long-termfollow-up [15]. Current treatments for LTC include strategies such as daily emollient application, intermittent use of TAT (TAT-based strategy: once or twice a week [15–18]), avoidance strategies, dietary interventions, and immunosuppressive drugs.

‘Add-on’ therapies, which are superimposed on standard TAT, seem promising for LTC. Systemic immunosuppressants are used as LTC add-on treatments, but they are reserved for the most severely affected patients because of safety concerns. In addition, neither immunosuppressants nor other strategies (with the exception of desensitization) [19] have been evaluated in the long term. LTC is one of the most important core outcome domains to be targeted in AD trials according to the HOME (Harmonising Outcome Measures for Eczema) recommendations [20]. Safe add-on therapies, rigorously evaluated for disease LTC, are therefore needed.

Phototherapy is a good candidate for the ‘in-between’ AD population, being widely used as a second-line treatment in AD with demonstrated efficacy [12]. However, only short-term control has been evaluated, and only intensive schedules of two or three sessions per week have been tested and are used in current practice. A novel phototherapy regimen enabling a trade-off between disease control, ultraviolet (UV)-induced risks, and patient acceptability is required for LTC of the disease. No serious short-term adverse events were collected in the review by Garritsen et al. [12], where the most common adverse event was xerosis.

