#### Exclusion criteria

Exclusion criteria: patients with AD known to be aggravated by UV exposure; indication for a systemic immunosuppressant in the next 2 years; any cause of contra-indication for vitamin D supplementation: granulomatosis flare, primary hyperparathyroidism; clinical suspicion of hypercalciuria; any contra-indication for artificial or solar photo-exposure including genetic disease predisposing to skin cancer, any history of skin cancer (melanoma, squamous and basal skin cancers), lupus, dermatomyositis, any other photosensitizing skin disease, photosensitizing medication; and more than 100 previous phototherapy sessions in their lifetime.

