#### Blinding

This study is conducted as open-label regarding phototherapy, since blinding cannot be implemented, but it is double-blind for vitamin D therapy.

Vitamin D: patients, investigators and outcome assessors will be blinded. Although it would have been possible to implement logistics with a blinded switch to placebo for patients reaching normal vitamin D levels, the absence of supplementation dose adaptation based on vitamin D serum level will help maintain the blinding.

Phototherapy: patients and investigators will not be blinded, and cannot be. We will address the problem of blinding with regard to phototherapy by masking the allocated treatment (phototherapy or observation) for the investigator in charge of scoring disease severity. However, some objective clues (e.g., tanning, if present) cannot be masked.

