For descriptive purposes, it is instructive to carry out an analysis based on a summary of the statistics (a quantity calculated from each curve), which can reflect important aspects of the problem at hand – we have chosen the area under the curve (AUC) and the mean amplitude of PO-SCORAD score ranges. Descriptive statistics (mean and standard deviation) of the PO-SCORAD for each visit will also be provided. Normal distribution is assumed in the modeling analysis for the primary outcomes (PO-SCORAD severity score over two 1-year periods; cumulate consumption of TAT during winter) and will be checked at this stage.

The main analysis will be based on the adjusted model and will follow the ‘intention to treat’ principle, namely all participants, as randomized, will be analyzed; outcome data obtained from all participants, regardless of protocol adherence, will be used. Mixed model techniques (PROC MIXED) will be applied.

The multiplicity adjustment strategy used is a hierarchical closed test procedure, where the primary endpoints are ordered as follows: (E1) repeat measures of the PO-SCORAD severity score over 1 year and (E2) cumulate consumption of TAT over winter. We will test E1 and E2 sequentially at the same two-sided level of 0.05; we will test E1 first, if it proves significant, will we test E2. A Wald test with Kenward–Roger degrees of freedom will be used.

No subgroup analyses nor interim analyses are planned.

For secondary analyses, we will use up to four measures per 1-year period, collected at each clinical visit (every 3 months), including investigator-based severity scores (Eczema Area and Severity Index, Severity of Atopic Dermatitis Index, Investigator Global Assessment), patient-reported severity and quality of life scores (Patient-Oriented Eczema Measure, Dermatology Life Quality Index), serum vitamin D levels, total IgE serum levels, weeks of satisfactory control, inter-visit cumulate consumption of TAT, and synthetic patient-reported satisfaction at the end of each winter.

All analyses will use procedures available in SAS software 9.4 (SAS Institute, Carry, NC, USA).

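### Mandatory study exit when systemic immunosuppressants are recommended causes outcome-dependent loss of follow-up, yet is presented as reducing attrition bias

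*Protocol article*

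**What the plan says.** The Discussion introduces a list with "we plan the following procedures to minimize attrition bias", and its first item is that "any participant who is recommended systemic immunosuppressants will discontinue the study". The wording is the study, not the study treatment, and nothing in the article provides for outcome collection afterwards.

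The Background ties the trigger to severity: "higher-end patients need systemic immunosuppressants", and as add-on treatments "they are reserved for the most severely affected patients because of safety concerns". The Exclusion criteria remove at entry anyone with an "indication for a systemic immunosuppressant in the next 2 years".

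Statistical methods commits to intention to treat: "all participants, as randomized, will be analyzed", and "outcome data obtained from all participants, regardless of protocol adherence, will be used". The primary outcomes are tested in order: repeated PO-SCORAD over a year (E1), then one cumulative count of tubes of topical anti-inflammatory treatment (TAT) per winter (E2). Under Blinding, vitamin D is double-blind. For the other factor, "Phototherapy: patients and investigators will not be blinded, and cannot be", although the investigator who scores severity is to be masked.

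**The concern.** A compulsory exit adds attrition; it cannot reduce it. Foreseeable candidates for systemic treatment are already excluded at entry, so a recommendation after randomisation mostly identifies patients whose control has newly failed. Long-term control is what the trial measures, so follow-up is lost because of the outcome.

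Three things are at stake.

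- Scores after exit are never collected, and no analysis plan can recover them. If more patients fail under placebo or observation, the comparison loses more of its worst scores on that side.
- E2 is one number per patient-winter, so an exit during winter leaves it incomplete.
- In the phototherapy crossover, an exit in year 1 removes the second winter and with it the within-patient contrast.

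For open-label phototherapy there is a further possibility: the decision to recommend systemic treatment could depend on which winter the patient is in.

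**Working it through.** **1. The passages side by side.** The trigger is a recommendation for a drug that the Background places at the severe end. The consequence is leaving the study. The stated purpose is less attrition bias. The purpose does not follow from the rule. The intention-to-treat text covers data that were obtained, so data up to exit are used and data after exit do not exist.

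**2. The plan's own figures (Sample size).** The parallel-arm total of 340 is halved: 340 / 2 = 170. Inflating for non-completion, 170 / (1 − 0.15) = 200, which matches the planned enrolment; 170 / (1 − 0.10) = 188.9, or 189, does not. The all-cause allowance of 10-15% is 20 to 30 of 200 patients. The 340 itself cannot be rebuilt, because the anticipated means are in an additional file that is not shown.

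**3. A benchmark for E1.** With SD 18, base correlation 0.6, decay 0.05 and 12 measures, the SD of a patient's mean is 14.27. At 80% power and two-sided 0.05, 170 per arm detects 2.8016 × 14.27 × √(2/170) = 4.34 points.

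**4. E1, phototherapy contrast, by simulation.** Assumed, not in the article: 24 measures, constant correlation 0.59, mean 45, exit when PO-SCORAD exceeds a threshold of 82 to 90, overall loss of about 5-14%. From the article: 200 patients, SD 18. The analysis is a mixed model on all data obtained, with 400 replicates. The SD of the estimate was 0.33 to 0.39, so the simulation error is about 0.02.

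| True effect | Triggering score recorded | Triggering score not recorded |
|---|---|---|
| −4.5 | −4.48 to −4.51 | −4.44 to −4.47 |
| −9 | −9.00 to −9.02 | −8.87 to −8.93 |

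Unrecorded, the attenuation is about 1-1.5% (for example 0.065 / 4.5 = 1.4%).

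**5. E1, vitamin D contrast, by simulation.** This comparison is between patients, so it is less protected.

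- 24 measures, correlation 0.59, true effect −4.5. Recorded: −4.41 to −4.51 at 4-12% exit. Unrecorded: −4.31 at 6.5% versus 4% exit (0.19 / 4.5 = 4%) and −4.17 at 12% versus 7% (0.33 / 4.5 = 7%).
- One year, 12 measures, the plan's correlation, assumed mean 45, exit above 80-90, true effect −4.34. Recorded: −4.33 to −4.36. Unrecorded: −3.75 to −4.15, that is 0.59 / 4.34 = 14% down to 0.19 / 4.34 = 4%.

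The unrecorded case is plausible because home PO-SCORAD is completed only every 4 weeks, so a flare can lead to a recommendation between two entries.

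**6. E2.** Suppose exits fall evenly over the winter, leavers use 1.5 to 2 times the average, and a truncated count is entered as if complete. Half of each leaver's use is then lost, and the mean difference shifts by 0.5 × (1.5 to 2) × (difference in exit rates). At 10% versus 5% exit this is 3.75-5% of mean consumption; at 15% versus 5% it is 7.5-10%. If the count were instead rescaled to a full winter at a constant rate of use, the shift would be zero. If use peaks just before exit, rescaling would overstate it. The sign and size therefore rest on handling that is not stated.

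**The case against.** Several points on the other side are sound.

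- A reader might infer that the rule contradicts the intention-to-treat statement. It does not, literally. That statement concerns data obtained; every randomised patient stays in the analysis, and the mixed model uses scores up to exit. It is later follow-up that is lost, not the patients.
- A reader might size the E1 bias as excess score times difference in exit rates. With assumed excesses of 9 or 18 points and rate differences of 0.05 or 0.10 this gives 0.45 to 1.8 points, or 10-40% of 4.34. That ignores the repeated measures, their correlation and the planned mixed model. In the crossover, each patient has one winter of each kind, so 10% plus 5%, or 15% plus 5%, means 15-20% lost from this cause alone, at or above the 10-15% planned from all causes.
- A reader might infer that failing patients will show falsely low TAT use. That holds only if truncated counts stand as full-winter totals, which no section says.
- Arm-dependent recommendation through unblinding cannot apply to vitamin D, which the Background calls the main trial. For phototherapy it is possible, but the article does not say who makes the recommendation.
- The rule is one clause in a condensed article. The full protocol may define what leaving the study means, and missing-data handling may sit in an analysis plan that is not shown.

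What remains is that the stated rationale runs the wrong way, and that an analysis plan cannot supply scores that were never collected.

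**Conclusion.** The defect stands in a limited form. The rule causes outcome-dependent loss of follow-up, is wrongly described as minimising attrition bias, and undercuts the intention-to-treat aim without literally contradicting it.

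For E1 the expected bias is toward no effect and modest: near zero when the triggering score is recorded, and about 1-14% attenuation when it is not, with the smaller values for the phototherapy crossover and the larger for vitamin D. These figures rest on the assumed mean, exit thresholds and exit rates above. E2 is the more exposed endpoint, with direction undetermined. A year-1 exit also costs the within-patient phototherapy contrast on which the halved sample size relies. This is a point that should be fixed, not one that invalidates the design.

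**What to change.** Reconcile the Discussion with Statistical methods by distinguishing stopping study treatment from leaving follow-up.

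- After a recommendation for systemic treatment, continue the 4-weekly home PO-SCORAD and the TAT counts unless the patient withdraws consent.
- Include these data in the intention-to-treat analysis.
- State how an incomplete winter TAT total is handled.
- Report the number and timing of such recommendations by arm, and for phototherapy by period.
- Add a sensitivity analysis that counts a recommendation as failure of control.
- Remove the claim that the exit rule reduces attrition bias.

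The cost is a short amendment. PO-SCORAD is already completed at home; tube counts may need the scheduled visits or a brief contact. The drawback is that scores after a systemic drug starts partly reflect that drug, which the sensitivity analysis addresses. Decisions on treatment stay with the clinicians and are unchanged. If the full protocol already continues follow-up, correcting the article's sentence is enough on that part.
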